### Study design: sample size and power calculations

Based on power analyses, the target sample size is 125 participants in each arm (treatment and control), meaning that there will be a target of 250 participants in total for the primary analyses at 6 months across the participating sites. To account for attrition of 25%, it is anticipated that up to 333 participants will be recruited into the baseline phase of the trial. It is estimated that 50% of people approached will decline to take part. Therefore, approximately 666 participants will be identified as eligible and screened.

We will use an approach based on a simple t-test for the between group comparison in the primary suicide outcome measure which is specifically designed to account for differential clustering or partial nesting between the two arms [49]. It is implemented using the command clsampsi- in Stata [50]. This approach requires the following assumptions:
Effect size: A clinically meaningful difference on the primary suicide outcome variable (ASIQ) from baseline to the 6 month follow-up time-point is estimated as a 16 point reduction, which corresponds to an effect size of 0.42, based on pilot data [30].Attrition: We are allowing for an attrition rate of 25% from baseline to final follow-up.Clustering: we account for clustering of outcomes within the participants sharing a therapist in the treatment arm with an ICC = 0.02.Random allocation: 1:1 random allocation, 0.05 significance level, and 80% statistical power.

For our proposed mediational analyses to test psychological mechanisms, a sample size of approximately 250 has greater than 80% power to detect a proportion mediated of 35%, and over 70% power to detect a proportion mediated of 30% (calculated using PowerMediation in R).

In sum, our sample size will have sufficient power for our proposed efficacy and mediation analyses.

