### Data analyses of the CARMS RCT

#### Analysis of the trial data to assess efficacy

A statistical analysis plan will be prepared before any analysis is undertaken, and agreed with the independent DMEC and TSC. Reporting will follow the CONSORT for Psychological and Social Interventions. All analyses and summary statistics will be conducted on the Intention-To-Treat (ITT) population which is defined as all participants randomised regardless of completion of therapy or withdrawal from the study. All analyses will be carried out at the end of the last follow-up assessments, and no interim analysis is planned.

Consideration will be given to potential biases arising from loss to follow-up.

Analyses will be conducted in Stata version 16 or later. Descriptive statistics within each randomised group will be presented for baseline values. These will include counts and percentages for binary and categorical variables, and means and standard deviations, or medians with lower and upper quartiles, for continuous variables, along with minimum and maximum values and counts of missing values. There will be no tests of statistical significance or confidence intervals for differences between randomised groups on any baseline variable.

Treatment effects on primary and secondary outcomes will be estimated using linear mixed models fitted to outcome variables at all time points. Fixed effects will be NHS site, anti-depressant use at baseline (yes/no), baseline assessment for the outcome under investigation, treatment, time and time*treatment interactions. Participant will be included as a random intercept to account for repeated measures. If the number of therapists is different from the number of NHS sites, we will include therapist as an additional random effect.

Marginal treatment effects will be estimated for primary outcome (ASIQ score at 6 months), and for primary and secondary outcomes at all other time points, and reported separately as adjusted mean differences in scores between the groups with 95% confidence intervals and 2-sided *p*-values. Cohen’s D effect sizes will be calculated as the adjusted mean difference of the outcome divided by the sample standard deviation of the outcome at baseline. These will be displayed in a forest plot showing the treatment effects on the primary and the secondary outcomes at 6 months.

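### Therapist clustering enters the primary model only when therapist and site counts differ, although the trial was sized for it unconditionally; if the counts match, the primary p-value is anti-conservative

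*Protocol article*

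**What the plan says.** The sample size section uses a t-test approach "which is specifically designed to account for differential clustering or partial nesting between the two arms". Among its assumptions it states: "we account for clustering of outcomes within the participants sharing a therapist in the treatment arm with an ICC = 0.02". Nothing there makes the clustering depend on how many therapists or sites there are.

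The section on the analysis of efficacy specifies a linear mixed model for all time points. On the fixed part it says: "Fixed effects will be NHS site, anti-depressant use at baseline (yes/no), baseline assessment for the outcome under investigation, treatment, time and time*treatment interactions". On the random part it says: "Participant will be included as a random intercept to account for repeated measures". Therapist is then added conditionally: "If the number of therapists is different from the number of NHS sites, we will include therapist as an additional random effect".

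The article gives neither the number of therapists nor the number of sites.

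**The concern.** When the two counts are equal, the primary model has a site main effect and a participant random intercept, and no term for therapist. The participant intercept handles repeated measures on one person. It does nothing for correlation between people who share a therapist.

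The likely reason for the rule is that, with one therapist per site, therapist would be aliased with site. That reasoning fails on two counts.

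1. Equal counts do not imply a one-to-one match. Five therapists and five sites are compatible with therapists covering several sites.
2. Even with a perfect match there is no aliasing. TAU participants have no trial therapist, and each site's TAU participants help to identify the site effect. A therapist effect in the therapy arm only is therefore a site-by-treatment component. The model has no such term, so the variance stays in the treatment contrast and the reported standard error leaves it out. The component is estimable, so nothing forces its omission.

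At stake are the standard error, confidence interval and p-value for ASIQ at 6 months. The secondary outcomes use the same model.

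**Working it through.** **Inputs from the sample size section.** 125 analysed per arm; effect size 0.42 (16 ASIQ points, so an implied SD of 16/0.42 = 38.1); therapist ICC 0.02 in the treatment arm; 1:1 allocation; significance level 0.05; power 80%. The efficacy section gives two-sided p-values. The number of therapists, k, is not stated, so a range is shown.

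**The plan's own figures.** Without clustering, d = 0.42 needs 89 per arm, and 125 per arm gives 91.3% power. With ICC 0.02, 125 per arm gives about 80% power at k = 3 by normal approximation (79.9%) or at k = 6 with Satterthwaite degrees of freedom (80.7%). The stated size is thus compatible with the stated assumptions for some k, but cannot be pinned down without it. Attrition: 250/0.75 = 333.3, which matches the target of up to 333.

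**Effect of omitting the therapist term.**

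- Mean therapist caseload: m = 125/k.
- Therapy-arm design effect: DE = 1 + (m − 1) × 0.02.
- True SE divided by reported SE: r = √((DE + 1)/2), because only one arm is clustered.
- Actual two-sided type I error at nominal 5%: 2 × (1 − Φ(1.96/r)).

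Example, k = 5: m = 25; DE = 1 + 24 × 0.02 = 1.48; r = √(2.48/2) = 1.114; 1.96/1.114 = 1.76; error 7.8%.

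| k | DE | r | Type I error |
|---|---|---|---|
| 3 | 1.813 | 1.186 | 9.8% |
| 4 | 1.605 | 1.141 | 8.6% |
| 5 | 1.480 | 1.114 | 7.8% |
| 6 | 1.397 | 1.095 | 7.3% |
| 8 | 1.292 | 1.071 | 6.7% |
| 10 | 1.230 | 1.056 | 6.3% |
| 20 | 1.105 | 1.026 | 5.6% |

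**Does the site effect rescue it?** This was simulated with about 250 participants, a single outcome, site fixed effects, therapist effects in the treated arm only and no therapist term.

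| Sites = therapists | One therapist per site (20,000 runs) | Equal counts, therapists across sites (10,000 runs) |
|---|---|---|
| 4 | 8.5% | 8.4% |
| 5 | 8.0% | 7.7% |
| 8 | 6.4% | 7.2% |
| 10 | 6.3% | 6.5% |

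With the ICC set to zero, the same code gave about 5% throughout. The site main effect does not remove the inflation, even under a perfect one-to-one match.

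**Sensitivity to the ICC (closed form, k = 3 to k = 20).** ICC 0.01: 7.4% to 5.3%. ICC 0.05: 16.8% to 6.5%.

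**Power once therapist is always modelled.** Let v_T = DE/125 and v_C = 1/125. The Satterthwaite degrees of freedom are (v_T + v_C)² / (v_T²/(k − 1) + v_C²/124). Power at d = 0.42 is then 60.5% (k = 3), 72.0% (4), 77.5% (5), 80.7% (6), 84.1% (8), 85.9% (10) and 89.0% (20).

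**The case against.** The strongest reply is that the harm is contingent. The term is dropped only if two unstated counts coincide; in every other case the protocol commits to a therapist random effect. The inflation is also modest when therapists are many, and the ICC of 0.02 is only a planning value. All of this stands. It limits the size and certainty of the harm, but it does not make the rule valid, because the rule expressly provides for the case in which it fails.

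A second reply is that the rule is a recognisable, if crude, guard against aliasing therapist with site. It is fair to credit that purpose, but for a therapist effect confined to one arm the aliasing does not arise.

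A third reply is that a statistical analysis plan is promised before any analysis. It may well settle the degrees-of-freedom method and the residual variance structure, and their absence here is no fault. The inclusion rule, however, is already written into the protocol: an analysis plan that follows it inherits the problem, and one that departs from it contradicts the published text.

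A reader might also infer that the other branch fails too, because TAU participants could be coded as one large therapist cluster, which would cost power. The documents do not support that. The efficacy section does not say how TAU participants are coded, the sample size section points to an effect in the treatment arm only, and such coding is commonly left to the analysis plan.

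**Conclusion.** The concern holds in a limited form. The equal-count condition is not a valid test of whether therapist clustering needs modelling, and it is inconsistent with the unconditional clustering assumption used to size the trial. If the counts match, the type I error of the primary comparison would be between about 9.8% (3 therapists) and 5.6% (20) instead of 5%. This assumes 125 analysed per arm, equal caseloads, a residual ICC of 0.02 and a single 6-month comparison.

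It would go too far to say that the primary p-value will be anti-conservative, since the article does not establish that the counts are equal. Nor does the calculation show that 125 per arm is wrong; that figure depends on the unstated number of therapists. This is a point that should be fixed, not one that invalidates the plan.

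**What to change.** Delete the condition. State that the model for the primary and secondary outcomes will always include a therapist random effect that applies to the therapy arm only and is zero for TAU participants, whatever the numbers of therapists and sites. In practice this is a therapist-level random coefficient on the treatment indicator with no therapist-level intercept. Add that inference will use a small-sample degrees-of-freedom correction such as Satterthwaite or Kenward-Roger, with details in the analysis plan. The analysis then matches the design assumed for the sample size.

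The edit is about a sentence and needs no new data beyond a record of which therapist treated each participant. The real cost is precision: the confidence interval widens when therapists are few, and with only about 3 to 5 of them power falls below the planned 80% (about 60% to 78% in the calculation above). That is the honest precision of the design, and omitting the term would hide it, not remove it.

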
##### Clinical variables

Mental health problems pertaining to psychosis, depression, and functioning, are measured in clinical interviews as follows: *Positive and Negative Syndrome Scale [PANSS]* [65], the *Psychotic Symptom Rating Scales [PSYRATS]* [66], the *Personal and Social Performance Scale [PSP]* [67] *and the Calgary Depression Scale [CDS]* [68]. The PANSS is the most widely used measure of positive, negative and general symptoms experienced by people with psychosis and was shown to have sound psychometric properties using a response analysis [69]. The PSYRATS shows excellent reliability across raters and has robust validity [66]. The PSP has excellent face validity and reliability with the majority of ratings taking place in those with schizophrenia [67]. The CDS was specifically designed for people with schizophrenia and was reported as having excellent reliability estimates [68].

Information about current medication for mental health problems (e.g., anti-psychotic and anti-depressant medication) will be recorded from self-reports and supplemented from clinical records where possible.

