We will allow for the presence of missing data under the assumption that the data are Missing At Random, conditional on the covariates in the model, and as a sensitivity analysis include other baseline measures as predictors of future loss to follow-up.

To account for the possible prognostic effect of anti-depressant medication on outcomes, we will include anti-depressant use at baseline (yes/no) as a stratifying factor. We acknowledge that use of anti-depressant medication after randomisation might account for a proportion of any observed treatment effect because it might lie on the causal pathway between randomisation and outcome but it is not targeted by the intervention itself. If there is a significant differential effect in the uptake of anti-depressant medication between the treatment and control groups, we will assess the role of anti-depressant medication as a mediator, in addition to our hypothesised target mediators.

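### Post-randomisation anti-depressant use is assessed as a mediator only if uptake differs significantly between arms; that test is weak at 125 per arm, and passing it biases the mediated effect upward on average

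*Protocol article*

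**What the plan says.** In the protocol article, under the analysis of the trial data to assess efficacy, the authors say that anti-depressant use after randomisation "might account for a proportion of any observed treatment effect because it might lie on the causal pathway between randomisation and outcome", and that the therapy does not target it. The next sentence sets a condition, "If there is a significant differential effect in the uptake of anti-depressant medication between the treatment and control groups", and only then "we will assess the role of anti-depressant medication as a mediator, in addition to our hypothesised target mediators".

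The condition comes with no named test, significance level, expected uptake or difference that would matter. The section on analysing mechanisms attaches no such condition to the hypothesised psychological mediators.

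The data for an unconditional analysis should exist. The section on clinical variables states: "Information about current medication for mental health problems (e.g., anti-psychotic and anti-depressant medication) will be recorded", from self-report supplemented by clinical records where possible. The section on the RCT design schedules clinical variables at baseline, 6 and 12 months.

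**The concern.** The article names a rival explanation for any benefit and then lets a significance test decide whether to examine it. This has two consequences.

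- **Condition not met.** Absence of significance is read as absence of the pathway. Whatever share the pathway has stays in the direct effect. It moves into the target mediators only if medication also changes, or is correlated with, those mediators.
- **Condition met.** The analysis is run only in trials where the observed uptake difference happened to be large enough. The uptake difference, and the mediated effect built on it, are then too large on average.

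The trial sets out to establish mechanisms as well as efficacy, so how the effect is divided between pathways matters. The power statement for mediation concerns the psychological mechanisms. Nothing in the article covers the power of the uptake test.

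**Working it through.** **Inputs from the article (sample size section).** The analysed number comes from "meaning that there will be a target of 250 participants in total for the primary analyses at 6 months", which is 125 per arm. Recruitment comes from "To account for attrition of 25%, it is anticipated that up to 333 participants will be recruited". Error rates come from "1:1 random allocation, 0.05 significance level, and 80% statistical power". The planned effect is 16 ASIQ points, or 0.42 SD, so the implied SD is 16 / 0.42 = 38.1. The therapist ICC is 0.02 in the treatment arm.

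**Assumptions.** Control-arm anti-depressant use at follow-up is not given, so 10% to 60% is tried. I take significant to mean p < 0.05 two-sided, as in the sample size section and the two-sided p-values of the efficacy analysis. The test is an unadjusted comparison of two proportions.

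**Step 1: the article's own figure.**
- Without clustering: n = 2(1.96 + 0.84)² / 0.42², about 89 per arm.
- With clustering in the therapy arm only, and an assumed 3 therapists: cluster size 125 / 3 = 41.7 and design effect 1 + 40.7 × 0.02 = 1.81. Power at 125 per arm is then 0.796. The figure of 125 is therefore reproduced closely, although the number of therapists is my assumption.
- Attrition: 250 / 0.75 = 333.3, which matches 333.

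**Step 2: chance that the condition is met.** Let p0 and p1 be the true proportions, d = p1 − p0, p̄ their mean and n = 125.

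Power ≈ Φ{ [d − 1.96·√(2p̄(1−p̄)/n)] / √([p0(1−p0) + p1(1−p1)]/n) }

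For 40% v 50%:
- √(2 × 0.45 × 0.55 / 125) = 0.0629, and 1.96 × 0.0629 = 0.123.
- √((0.24 + 0.25) / 125) = 0.0626.
- Φ((0.100 − 0.123) / 0.0626) = 0.355.

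| True difference | Control use 10% | Control use 20–60% |
|---|---|---|
| 5 points | 22% | 12–16% |
| 10 points | 60% | 36–45% |
| 15 points | 88% | 66–76% |
| 20 points | 98% | 89–94% |

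Power reaches 50% at 8.7 points when control use is 10%, and at 10.8 to 12.4 points when it is 20% to 60%. Power of 80% needs 13 points and 16 to 18 points respectively. With no attrition (166 per arm) and control use of 20% to 60%, power at 10 points is 45% to 56%.

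**Step 3: what a non-significant result leaves open.** If 40% v 50% is observed, the 95% interval is 0.10 ± 1.96 × 0.0626, or about −2 to +22 points. The pathway would be dropped with a 20-point difference still compatible with the data.

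**Step 4: bias when the condition is met.** Simulation with 200,000 trials per cell gives the mean observed uptake difference among significant trials, divided by the true difference:

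| True difference | Control use 10% | Control use 20–60% |
|---|---|---|
| 5 points | 2.1 | 2.6–2.9 |
| 10 points | 1.28 | 1.5–1.7 |
| 15 points | 1.07 | 1.15–1.23 |
| 20 points | 1.01 | 1.04–1.07 |

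The mediated effect is the uptake difference times the medication-to-ASIQ effect, so it inherits this bias. Suppose the medication effect is −10 ASIQ points, control use is 50% and the true difference is 10 points. The true mediated effect is then −1.00. If the model is always run, the simulated mean is −1.01. If it is run only after significance (about 35% of trials), the mean is −1.67.

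**Step 5: size of the share at stake.** Suppose anti-depressant use moved ASIQ by the full 16 points, which is generous. An undetected 12-point imbalance would then carry 0.12 × 16 = 1.9 points, or 1.9 / 16 = 12% of the planned effect and 1.9 / 38.1 = 0.05 SD. At half that drug effect it is about 1 point, or 6%.

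**The case against.** The strongest objection is that the condition tends to exclude the pathway only when it is small. That largely stands. A small uptake difference gives a small mediated effect unless the drug effect is large, and a 6% to 12% share would not be reliably detected by an unconditional model either. The article claims only just over 70% power for a proportion mediated of 30%. An estimate with its interval would still say more than silence.

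A second objection is that the uptake test may be more powerful than assumed. Randomisation is stratified on baseline anti-depressant use, so an adjusted test is plausible. With an assumed correlation of 0.7 between baseline and follow-up use, power is about 20% at 5 points and 60% at 10, and the 50% point is near 9. This shifts the figures but does not rescue the rule.

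A third objection is that later anti-depressant use is not randomised, and worsening suicidality may itself prompt prescribing. The medication-to-ASIQ path can therefore be biased whether or not the condition is kept. This stands, and the fix has to carry it as a caveat. The mechanism section does plan methods intended to allow for hidden confounders.

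A reader might go further than the documents allow in three ways:
- **That the pathway will usually go untested.** This depends on a true uptake difference that the article does not give. At 15 to 20 points the condition is met in about two thirds of trials or more.
- **That the pathway will be overstated whenever it is tested.** The bias is an average, need not hold in a single trial, and is slight at 20 points.
- **That differences below 9 to 12 points can never trigger the analysis.** This is true only of observed differences. A true 5-point difference triggers it in 12% to 22% of trials.

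**Conclusion.** The point holds in a limited form. The protocol article itself fixes a significance condition on a pathway that it says may carry part of the effect, so this is not a detail left to the analysis plan. At 125 per arm the condition is more likely than not to fail unless true uptake differs by more than roughly 9 to 12 points, and failing it does not show that the pathway is absent. Passing it inflates the estimates on average, appreciably near 10 points and hardly at all at 20.

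These figures rest on assumed control-arm use of 10% to 60%, an unadjusted two-sided 0.05 test and the target analysed number. The primary outcome and the intention-to-treat efficacy estimate are not affected. What is affected is the attribution of benefit to mechanisms, and the 12% share in Step 5 is an illustration under a generous drug effect, not an estimate. The change is worth making because it is cheap, not because the trial's main conclusion is at risk.

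**What to change.** Delete the significance condition and replace it with text along these lines:

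*Anti-depressant use after randomisation will be reported by arm at 6 and 12 months, with the difference and its 95% confidence interval. Its mediated effect on 6-month ASIQ will be estimated with a 95% confidence interval whatever the p-value for uptake, adjusting for baseline anti-depressant use and baseline ASIQ. This is a supplementary analysis; the medication-to-outcome path is not randomised and may be confounded by indication.*

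The cost is one extra model on data already planned for collection, an interval that may be wide, and the need to keep the caveat on confounding wherever the result is reported. Removing the condition removes the selection bias only; it does not remove that confounding.
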